The findings of the Kimberley validation study [13] have led to endorsement of the KMMS by the Kimberley Aboriginal Health Planning Forum (KAHPF) as the recommended perinatal depression and anxiety screening tool for all Aboriginal and Torres Strait Islander women in the Kimberley region [18]. To better embed the KMMS into routine clinical practice we need to understand ‘real world’ KMMS utilisation/implementation, such as quality, clinical support required and acceptability. We also need to test the validity of the KMMS at a population level, i.e., ‘revalidate’ the KMMS in a larger Kimberley sample via a real world implementation study. Other regions in Australia have also expressed interest in using the KMMS with Aboriginal and Torres Strait Islander women during the perinatal period. Before recommendations for wider use can be made, we need to test for applicability in other regions. This paper outlines the protocol for evaluating the process of implementation and establishing the ‘real world’ quality, validity and acceptability of the KMMS in the Kimberley, Pilbara and Far North Queensland (FNQ) regions of Australia.

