## Methods/design

### Objectives

The primary objectives of this study are to 1) evaluate the implementation and real-world performance of the KMMS in the Kimberley; 2) test the validity of the KMMS in the Pilbara and FNQ; and 3) assess the acceptability of the KMMS for Aboriginal and Torres Strait Islander women and their health professionals across all sites, i.e. Kimberley, Pilbara and FNQ.

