### Outcome measures

Primary outcomes:
Diagnostic accuracy of the KMMS as a screening tool for perinatal depression and anxiety assessed by comparing results of the KMMS with the DMT.Acceptability of the KMMS for all sites assessed primarily through the qualitative methodology of phenomenology supplemented with descriptive statistical analysis.Implementation of the KMMS in the Kimberley assessed using a process evaluation methodology framed by the DSF.

Secondary outcomes:
Patterns of change identified in KMMS risk for women who have more than one KMMS assessment.Variations in DMT diagnosis determined with KMMS assessment overall score based on if the DMT was conducted blinded or not.KMMS quality and appropriateness identified based on the findings of the KMMS quality review panels.

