### Sample size calculation

We plan to recruit an equal number of antenatal and postnatal women. The data from antenatal and postnatal women will be pooled for the main analysis, as there was no significant difference in KMMS or study GP assessments between antenatal and postnatal participants in the Kimberley validation study [13]. If there is no significant difference between the data from the three regions, these data will also be pooled.

For the validation/revalidation study, assuming there is a minimum sensitivity of 83% for screening for perinatal depression and anxiety and prevalence is at least 25% (based on the Kimberley validation study), using calculations by Buderer [32] a sample size of 868 paired KMMS and DMT assessments will detect a two-tailed 95% CI with a maximum width of ±5% (i.e., if sensitivity 83, 95% CI 78–88%). This is at the upper end of reported sensitivities for the EPDS compared to a reference standard assessment (59–100%) [33].

Based on the Kimberley validation study [13], we expect 65% of KMMS assessments to be referred for DMT and that at least 75% of the participants who are referred will have both the KMMS and DMT assessments completed (i.e., require 1780 KMMS to obtain 868 paired assessments). For the secondary analysis to determine changes in KMMS risk, we aim to assess as many participants as possible both antenatally and postnatally. As a conservative estimate, we will assume that at least 60% of participants will have KMMS administered at both time points. Recruiting 890 antenatal women (50% of the 1780 KMMS required) should provide at least 534 paired antenatal/postnatal KMMS assessments. In addition, approximately 356 women will be recruited postnatally to ensure that we have 890 antenatal and 890 postnatal KMMS assessments required for the main sample size calculation. Therefore, we initially aimed to recruit 1246 women (890 in the antenatal period and 356 women postnatally) to provide 868 paired KMMS / DMT assessments and 534 paired antenatal/postnatal KMMS assessments.

The complexity of establishing a partnership project across three remote regional areas has taken longer than anticipated; as such a revised sample size is 700 women across all three regions. Assuming 442 of the 700 women have paired KMMS and DMT assessments, this would allow us to detect a two-tailed 95% CI with a maximum width of ±7% (i.e., if sensitivity 83, 95% CI 76–90%).

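### Regions are pooled on a non-significant test of unspecified data, although validity in the Pilbara and FNQ is a primary objective of its own

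*Protocol article*

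**What the plan says.** The Objectives section lists, as the second of three primary objectives, to "test the validity of the KMMS in the Pilbara and FNQ". The Background gives the reason: "Before recommendations for wider use can be made, we need to test for applicability in other regions". The first primary outcome is "Diagnostic accuracy of the KMMS as a screening tool for perinatal depression and anxiety assessed by comparing results of the KMMS with the DMT".

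The Sample size calculation section sizes the study for one sensitivity estimate over all regions: 868 pairs of Kimberley Mum's Mood Scale (KMMS) and Diagnosis and Management Tool (DMT) assessments for ±5 points, revised to 442 pairs for ±7 points. On regions it then says: "If there is no significant difference between the data from the three regions, these data will also be pooled". It gives no test, no alpha, no margin, no regional split and no minimum number per region.

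Under Quantitative analysis, the regional comparisons named are χ² and Mann–Whitney tests of participant characteristics. No regional comparison of sensitivity or specificity is named.

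Antenatal and postnatal data are handled differently. They are pooled for the main analysis without any condition, "as there was no significant difference in KMMS or study GP assessments between antenatal and postnatal participants in the Kimberley validation study".

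**The concern.** The rule treats failure to reject as evidence that the regions are alike. A small sample fails to reject easily, so the fewer women the new regions contribute, the more readily the condition for pooling is met. Cutting the target from 868 to 442 pairs pushes in that direction.

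The rule fails on either reading of what is tested. If the trigger is the comparison of characteristics, it does not address whether the tool classifies women equally well in each region: women can be similar in age or parity while the tool performs differently, and the reverse. If the trigger is a test on accuracy, the sample is small for it.

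The study is meant to inform whether the KMMS can be used outside the Kimberley. Under the rule, a pooled figure could stand for a region whose sensitivity is materially lower.

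**Working it through.** **1. The article's own sample sizes.** Inputs from the Sample size calculation section: sensitivity 0.83, prevalence 0.25, two-sided 95%. Formula: pairs = [1.96² × Se(1 − Se) / d²] / prevalence.
- d = 0.05: 3.8416 × 0.1411 / 0.0025 = 216.8 cases; / 0.25 = 867 pairs, or 868 if cases are first rounded up to 217 (217 × 4 = 868).
- d = 0.07: 3.8416 × 0.1411 / 0.0049 = 110.6 cases; / 0.25 = 442 pairs.

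Both figures reproduce. Both are for all regions together.

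**2. Prevalence among pairs.** All moderate- or high-risk women but only a sample of low-risk women are referred for the DMT, so prevalence among pairs can exceed 25%. Using 25% prevalence, sensitivity 83%, specificity 87% (Background) and 65% referral:
- moderate/high risk: 0.25 × 0.83 + 0.75 × 0.13 = 0.2075 + 0.0975 = 0.305
- low risk: 0.695; fraction of these referred: (0.65 − 0.305) / 0.695 = 0.496
- cases among those referred: 0.2075 + 0.25 × 0.17 × 0.496 = 0.2286
- prevalence among those referred: 0.2286 / 0.65 = 0.35

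If DMT completion is equal across risk groups, 442 pairs contain about 442 × 0.35 = 155 cases, against about 110 at 25%. I carry both, and keep 83% as the sensitivity among pairs, as the article's own calculation does.

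**3. Chance that a regional test detects a difference.** Assumptions not in the article: a three-region Pearson chi-square on sensitivity among cases, alpha 0.05, and a split between equal and 60/20/20 (Kimberley largest). Power is by simulation. One region has sensitivity 68% (a new region in the uneven split); the others have 83%.

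| Prevalence among pairs | Cases per region | Power | Pooled despite the difference |
|---|---|---|---|
| 25% | 37/37/37 | 34% | 66% |
| 25% | 66/22/22 | 28% | 72% |
| 35% | 52/52/52 | 45% | 55% |
| 35% | 93/31/31 | about 38% (37–38% between runs) | about 62% |

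At 25% prevalence, the mean pooled sensitivity when the test is non-significant is 78% (equal split) or 80% (60/20/20). If both new regions were at 68% with 66/22/22 cases, power is 38% and the mean pooled figure is 77%, inside the 76–90% interval that the article gives as its planning example. With 93/31/31 cases, power for that scenario is about 50%.

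**4. Where the test does better.** Sensitivity 20 points lower in one region, equal split: power 53% (37 cases per region) or 69% (52 per region). Specificity 72% against 87% in one region, equal split: about 79% (96 non-cases per region) to 84% (about 110 per region).

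**5. Precision within one region.** Half-width = 1.96 × √(0.83 × 0.17 / cases):
- 52 cases: ±10 points
- 37 cases: ±12 points
- 31 cases: ±13 points
- 22 cases: ±16 points

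The stated ±7 points corresponds to about 110 cases, that is, to the pool.

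**The case against.** The strongest reply is that the article never says a pooled estimate replaces the regional ones. Objective 2 stays separate, the Pilbara and FNQ validation study has its own heading, and regional tables may sit in a full protocol or analysis plan that is not shown. This stands against a reading that a reader might infer, namely that objective 2 will be declared met on the pooled figure. The documents do not say so. What remains is that the published rule, followed as written, permits it, and that nothing in the article commits to regional accuracy estimates once pooling has occurred.

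Second, the power figures belong to a test that the article does not name. This also stands. The pooling percentages describe a hypothetical test under assumed splits and are not a property of the documented plan. They show only that, even on the reading most favourable to the rule, non-significance would be weak evidence.

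Third, a reader might conclude that the test would rarely detect any real difference. That goes too far. It is fair for sensitivity losses of around 10 to 15 points, but not for 20-point losses or for specificity differences of 15 points.

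Fourth, a reader might extend the criticism to antenatal/postnatal pooling. That pooling is fixed in advance from earlier data and is not conditional on a test in this study. The earlier comparison, in a 91-woman study, is described as one of assessment results and so says little about accuracy, but prespecifying a pooled main analysis is defensible.

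**Conclusion.** The concern holds. The article states a rule that pools regions on non-significance, leaves open which data are tested, and names regional tests only of characteristics, while a primary objective is region-specific. If the test were on sensitivity, a true 15-point loss in one region would go undetected, and the regions would be pooled, in about 55–72% of studies. This rests on 442 pairs, alpha 0.05, splits from equal to 60/20/20, and 25–35% prevalence among pairs. The sample size arithmetic is correct; the fault is in the pooling rule and in quoting precision only for the pool.

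**What to change.** - Delete the significance condition on regional pooling.
- Report sensitivity and specificity with 95% CIs for each region, whatever any test shows.
- State that the answer to objective 2 rests on the Pilbara and FNQ estimates.
- Give the pooled estimate as a region-stratified summary regardless of p-values, with between-region differences and their CIs.
- State that ±7 points applies only to the pool, and that region-level half-widths for sensitivity are expected to be about ±10 to ±16 points, depending on the split and the prevalence among pairs.
- Optionally, also show accuracy by antenatal/postnatal status.

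The cost is wording and a few extra table rows, with no change to recruitment or data collection. The downside is that the regional intervals will be visibly wide, which a reader deciding on use outside the Kimberley needs to see.

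### Pooling the three regions on a non-significant test treats absence of evidence as equal accuracy, and the plan does not commit to the regional estimates that objective 2 needs

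*Protocol article*

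**What the plan says.** The pooling rule is in the protocol article under Sample size calculation: "If there is no significant difference between the data from the three regions, these data will also be pooled". The rule names no variable, significance level or equivalence margin.

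Under Objectives, the regions have different questions. Objective 1 concerns implementation and real-world performance in the Kimberley. Objective 2 is to "test the validity of the KMMS in the Pilbara and FNQ". The Background gives the reason: "Before recommendations for wider use can be made, we need to test for applicability in other regions".

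Precision is given only for the total. The first target was 868 paired KMMS and DMT assessments, for ±5 points around a sensitivity of 83%. It was later reduced: "a revised sample size is 700 women across all three regions". The precision statement then reads "Assuming 442 of the 700 women have paired KMMS and DMT assessments", giving ±7 points (76–90%). No regional numbers or regional precision are stated.

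The Quantitative analysis section plans ROC curves, sensitivity and specificity without saying whether these are given by region. The regional comparison it describes is of participant characteristics.

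**The concern.** A non-significant difference does not show that the regions have the same accuracy. With few diagnosed women per region, it is a common result even when one region is materially worse. The rule makes that result the condition for merging the data.

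The KMMS was developed and first validated in the Kimberley, so whether it carries over to the Pilbara and Far North Queensland is the open question. A single figure that includes Kimberley women does not answer it. If one region's sensitivity is well below the rest, the pooled figure can still look acceptable. A recommendation for wider use could then rest on it while cases are being missed in that region.

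The stated ±7 points depends on pooling. If the test refuses pooling, the article gives no precision for the accuracy outcome in any region.

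**Working it through.** **Inputs from the article (Sample size calculation):** sensitivity 83%, prevalence 25%, two-sided 95% confidence interval, 868 pairs at first and 442 after revision.

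**Inputs assumed, because the article does not give them:** a three-group chi-square test on sensitivity at 5%, and four splits of the diagnosed women across regions.

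**Step 1. Reproduce the plan's figures.** Pairs needed = 1.96² × Se × (1 − Se) / d² / prevalence.
- d = 0.05: 1.96² × 0.83 × 0.17 / 0.0025 = 216.8 cases; / 0.25 = 867.2 pairs (stated: 868).
- d = 0.07: 1.96² × 0.83 × 0.17 / 0.0049 = 110.6 cases; / 0.25 = 442.5 pairs (stated: 442).

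Both figures reproduce. The ±7 points therefore rests on all of the roughly 110 diagnosed women (442 × 0.25 = 110.5) being analysed together.

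**Step 2. How often the test would miss a weaker region.** The chi-square test was simulated with two regions at 83% and one of the smaller regions (any one, in the equal split) lower. The chance of pooling is 1 minus the power. The pooled sensitivity is the case-weighted mean; for example, with 55/28/28 and one region at 63%, (83 × 0.83 + 28 × 0.63) / 111 = 78.0%.

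| Cases per region | Power, 63% | Pooled Se, 63% | Power, 70% | Pooled Se, 70% | Power, 50% |
|---|---|---|---|---|---|
| 37/37/37 | 53% | 76.3% | 27% | 78.7% | 91% |
| 55/28/28 | 49% | 78.0% | 25% | 79.7% | 87% |
| 66/22/22 | 43% | 79.0% | 23% | 80.4% | 81% |
| 77/16/16 | 37% | 80.1% | 20% | 81.1% | 73% |

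- One region at 63%: missed in 47–63% of studies.
- One region at 70%: missed in 73–80%.
- One region at 50%: missed in 9–27%.
- No true difference: pooled in about 95%.

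In the 63% and 70% cases the pooled figure is about 76–81%. This lies inside the planned 76–90% interval, so it would not in itself draw attention to the weak region.

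**Step 3. Regional precision.** Half-width = 1.96 × √(0.83 × 0.17 / n).
- A third of the cases (n ≈ 37): ±12.1 points.
- A fifth of the cases (n ≈ 22): ±15.7 points.
- All cases (n = 110.5): ±7.0 points.

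**The case against.** The strongest reply is that the article says the data will be pooled, not that regional results will be withheld. It is organised by region, with a Kimberley revalidation study and a separate Pilbara and Far North Queensland validation study, and a fuller analysis plan may tabulate each region. This stands. A reader might infer that regional estimates are suppressed, and the text does not say so. What remains is that the article states a pooling rule and makes no commitment to regional accuracy.

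A second reply is that the tested variable and its significance level are details that an article may leave to the analysis plan. That is fair, and their absence is not the point here. The point is that non-significance is fixed as the criterion.

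A third is that the power figures are conditional. They cover sensitivity only. Specificity rests on about 330 women without a diagnosis (442 − 110 ≈ 332), so a regional difference there is easier to detect. Prevalence is stated as at least 25%, and only a proportion of low-risk women are referred for the DMT, so the pairs may contain more cases. At an assumed 35%, power for the 63% case rises to 57–69% over the three less uneven splits. That softens the size of the problem, but a region at 63% would still be missed in 31–43% of studies.

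A fourth is that the ±7 points is already tied to the total over the three regions. It is, but the article does not say what it becomes when the regions are not pooled.

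**Conclusion.** The point holds. The rule takes a non-significant test as sufficient ground for merging regions, while objective 2 asks about two of those regions and no regional accuracy estimate is promised. Under the assumed splits and a 5% test, a region at 63% is missed about half the time (47–63%) and a region at 70% in about three studies out of four (73–80%), with a pooled sensitivity of about 76–81%.

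Two stronger readings should be resisted. First, a reader might infer that any failing region would probably be hidden. At 63% the outcome is close to a coin toss, and at 50% the test would detect the difference in 73–91% of studies. Second, a reader might infer that Kimberley women would dominate the pooled figure. The article gives no regional split, so this is unsupported. It is also not needed: with an equal split, a region at 63% still gives a pooled figure of about 76%.

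**What to change.** In Sample size calculation and in Quantitative analysis:

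- Remove the significance test as the condition for regional reporting.
- State that sensitivity and specificity are reported for the Kimberley, the Pilbara and Far North Queensland with 95% confidence intervals, whatever any test shows, and that these estimates answer objectives 1 and 2.
- Present the pooled estimate beside them as an additional overall summary.
- State that ±7 points applies to the pooled sample only, and give regional half-widths computed from the sponsor's own expected regional numbers. The ±12 points (a third of the cases) and ±16 points (a fifth) above are illustrations, not values to copy.

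The cost is wording in two sections and one additional table. No new data are needed. The drawback is that the regional intervals will be visibly wide, which shows how much the study can say about each region.

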### The KMMS

Part 1 of the KMMS (modified version of the EPDS) includes 10 close-ended questions using regionally appropriate language and graphics. It is an important way to introduce concepts and language around perinatal depression and anxiety, with which women may be unfamiliar [2, 12].

Part 2 is a psychosocial yarning tool [15, 16]. The domains covered in Part 2 include: support; stressors; self-esteem; childhood experiences; relationships; substance use; and social, emotional and cultural wellbeing. Part 2 aims to identify protective and risk factors that may positively or negatively influence a woman’s sense of wellbeing and risk of perinatal depression or anxiety. Health professionals are provided with open-ended prompts to help facilitate the yarn (Additional file 2) [19].

After the KMMS is completed, health professionals then use their clinical judgement and experience to interpret Part 1 and Part 2 to determine a woman’s overall risk of perinatal depression and anxiety. Categories are: low risk (self-care recommended); moderate risk (clinical assessment within 1 week); and high risk (clinical assessment within 72 h). Any concerns regarding a woman’s risk of harm to herself or others (as raised in Part 1, question 10; Additional file 3) requires immediate action in accordance with the health service policies/protocols.

In the Kimberley it is recommended regional practice for all Aboriginal women to be screened with the KMMS (18) with the same frequency and timing as the national EPDS screening schedule [4]. When repeating screening on the same woman during the same perinatal period, a new Part 1 is completed; however, the yarn in the original Part 2 is continued as opposed to starting Part 2 from the beginning. It is recommended practice for those scoring moderate or high risk on the KMMS at any stage to have further clinical assessment by a general practitioner (GP) or mental health professional [18].

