#### KMMS quality review

Systematic and retrospective investigation of patient medical records has long been used in quality assessment and improvement studies, professional education and training, and as an assessment of patient care initiatives [26–29]. This study will review the quality and appropriateness of KMMS and DMT assessments from all sites via two separate panel processes (Additional files 5 and 6).

The panels will convene every 3 months and will consist of a minimum of four members who have relevant clinical expertise and are sufficiently impartial to the study [29], i.e. health professionals not engaged in the administration of the KMMS or the DMT. The panels will be convened by a member of the research team. A minimum of nine and maximum of 12 files will be selected by the KMMS research team and reviewed by the panel at each meeting. A quota sampling strategy [26] will be used to select the files to ensure the panels are reviewing a spread of KMMS/DMT results, antenatal and postnatal women, health professionals, and health services.

Overall findings from each panel will be disseminated back to partner health services as a quality initiative. Where required, additional training and support will be offered to health services to ensure that Aboriginal and Torres Strait Islander women are receiving appropriate care and support via the KMMS and the medical files and records reflect the service provided.

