### Data analyses

#### Quantitative analysis

KMMS validation/revalidation internal consistency of Part 1 will be determined using Cronbach’s alpha [38]. Equivalence for identifying risk of depression and anxiety compared to the DMT will be determined from receiver operating characteristic curves. Sensitivity and specificity will be determined based on these cut-points.

Differences in characteristics between antenatal and postnatal participants, participants who are or are not diagnosed with depressive and/or anxiety disorders, and participants from different regions will be compared using χ^2^ tests for categorical data and Mann–Whitney tests for continuous non-parametric data. Change in KMMS risk (from low to moderate/high, or vice versa) will be compared using McNemar’s test. Descriptive statistical analysis will be used when assessing trends and patterns in user acceptability.

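### The ±7% precision and the ordinary χ2 comparison of regions treat women as independent, although the overall KMMS risk is a rater's judgement: a modest loss for sensitivity, potentially a larger one for a regional test

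*Protocol article*

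**What the plan says.** **How the index result arises.** Under The KMMS, health professionals "use their clinical judgement and experience to interpret Part 1 and Part 2 to determine" the woman's overall risk as low, moderate or high. Under Administering the KMMS, the raters are trained staff of the partner services.

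**Precision.** Under Sample size calculation, the inputs are sensitivity, "assuming there is a minimum sensitivity of 83% for screening for perinatal depression and anxiety", and prevalence, "prevalence is at least 25% (based on the Kimberley validation study"). The initial target was "a sample size of 868 paired KMMS and DMT assessments will detect a two-tailed 95% CI with a maximum width of ±5" percentage points. After the reduction to 700 women, 442 pairs are assumed and "this would allow us to detect a two-tailed 95% CI with a maximum width of ±7" percentage points. No ICC, design effect or rater count is given.

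**Regions.** The same section sets the pooling rule: "If there is no significant difference between the data from the three regions, these data will also be pooled". It names neither a test nor a variable. Under Quantitative analysis, characteristics of "participants from different regions will be compared using χ^2^ tests for categorical data", with Mann–Whitney tests for continuous data.

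**The concern.** A rater who is strict or lenient at the boundary between low and moderate risk carries that tendency to every woman she rates, and raters sit within a service and a region. Results from women with the same rater then hold less information than the same number of independent results. This is separate from one woman contributing two assessments: it remains if each woman is assessed once.

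Two things are at stake. Diagnostic accuracy is the first primary outcome, and its stated precision treats variation between raters as zero, although that variation is part of the real-world performance under study. Also, a regional comparison of a rater-assigned result can come out significant because the regions have different raters. If that comparison governs pooling, the study could be split into three on a false signal, and each region would have only a fraction of the 442 pairs.

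**Working it through.** **Step 1: reproduce the plan's figures.** Inputs from Sample size calculation: sensitivity 0.83, prevalence 0.25, z = 1.96.
- Initial target: 1.96² × 0.83 × 0.17 / 0.05² = 216.8, rounded up to 217 cases; 217 / 0.25 = 868 pairs, as stated.
- Revised target: 442 × 0.25 = 110.5 cases; 1.96 × √(0.83 × 0.17 / 110.5) = 7.00%, as stated.

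Both figures come from the simple binomial variance, so no allowance for shared raters is built in.

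**Step 2: assumptions.** The article gives neither an ICC nor a rater count. I take ICC 0.05 (range 0.02 to 0.10) and 18 to 100 raters. The lower numbers come from the 6 to 12 administrators per region to be interviewed (Acceptability of the KMMS), times three regions. Those are a subset of the raters, so larger counts must be shown too.

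**Step 3: formulas.** With equal workloads, the design effect is DE = 1 + (m − 1) × ICC.
- Sensitivity: m = 110.5 cases / raters, and half-width = 7.00% × √DE.
- Three-region χ2 (2 df) on a rater-assigned result, with raters nested in region: m = 700 women / raters, and true size = P(χ2 > 5.99/DE) = exp(−2.996/DE).

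**Step 4: results at ICC 0.05, equal workloads.**

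| Raters | Cases per rater | DE | Sensitivity half-width | Women per rater | DE | True size of nominal 5% χ2 |
|---|---|---|---|---|---|---|
| 18 | 6.1 | 1.26 | ±7.85% | 38.9 | 2.89 | 36% |
| 30 | 3.7 | 1.13 | ±7.46% | 23.3 | 2.12 | 24% |
| 36 | 3.1 | 1.10 | ±7.36% | 19.4 | 1.92 | 21% |
| 60 | 1.8 | 1.04 | ±7.15% | 11.7 | 1.53 | 14% |
| 100 | 1.1 | 1.01 | ±7.02% | 7.0 | 1.30 | 10% |

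A beta-binomial simulation (20,000 runs) gave 24.3% for 30 raters and 13.9% for 60, which agrees with the formula.

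**Step 5: sensitivity to the assumptions.**
- ICC 0.02 to 0.10, equal workloads: half-width ±7.2% to ±7.9% with 30 raters, ±7.1% to ±7.3% with 60, and ±7.0% with 100. χ2 size 12.6% to 39.6%, 8.5% to 23.5% and 6.9% to 15.4% respectively.
- Unequal workloads (coefficient of variation 0.8; m is replaced by (1 + 0.8²)m in DE), ICC 0.05: ±7.84% and 35% with 30 raters, ±7.35% and 21% with 60, ±7.14% and 14% with 100.
- A comparison restricted to the 442 pairs, ICC 0.05, equal workloads: size about 17% with 30 raters and 10% with 60.

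The effect on sensitivity is small because only about 110 diagnosed women enter it, so each rater contributes few. The regional test suffers more because all of a rater's women count.

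**The case against.** **The number of women per rater is an inference.** The article says that trained service staff administer the KMMS. It does not say how many women each one screens. Training is offered to all perinatal health professionals in partner services, and the workforce is described as having high turnover and much temporary staffing; both point to more raters than the interview quota. This stands. It limits the size of the effect, not its direction.

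**A fixed restatement to ±8%.** A reader might infer that the stated precision should simply become ±8%. The documents do not support that: the value combines an assumed ICC with a rater count taken from an interview subset, and with 60 to 100 raters the half-width stays close to ±7%.

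**The χ2 test as the pooling test.** A reader might infer that the χ2 tests decide pooling. The article does not connect the two: χ2 is assigned to participants' characteristics, and the pooling rule names no test. The inflation computed above applies to rater-assigned results such as overall KMMS risk. It does not apply to a characteristic such as age, unless that also clusters by service.

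**A false-positive rate of 34–49%.** Such figures can be simulated, but only with 18 to 36 raters and unequal workloads. They should not be presented as what the plan implies.

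**The analysis intervals.** A reader might infer that the reported 95% intervals will under-cover. The article names no interval method, and an analysis plan that is not shown could use robust or bootstrap variance. It also claims no precision for specificity. What does not depend on any such plan is the sample size statement, which is complete as printed and assumes independence.

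**Conclusion.** The point holds in limited form. The ±5% and ±7% are independent-binomial figures for an index test that rests on a rater's judgement, and the only regional test named for categorical data takes no account of shared raters or services. With any positive within-rater correlation and more than one case per rater, ±7% is a best case. The loss on sensitivity is modest at ICC 0.05: under one percentage point with 18 or more equally loaded raters, and negligible with 100.

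The more important consequence is conditional. If an ordinary χ2 on a rater-assigned result is used for the pooling rule, regions would be declared different too often. At ICC 0.05 with equal workloads the rate is about 10% to 24% for 100 to 30 raters, instead of 5%. All sizes rest on an ICC and rater counts that the article does not give. This is a worthwhile low-cost improvement and does not undermine the design.

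**What to change.** - Compute confidence intervals for sensitivity, specificity and AUC with variance clustered on the administering health professional, or on health service where the administrator is not recorded (cluster-robust standard errors or a cluster bootstrap).
- Compare overall KMMS risk and other rater-assigned results between regions with a cluster-robust or mixed logistic model in place of the ordinary χ2, and name that model as the basis of the pooling decision.
- Add to the sample size section that ±7% assumes independent women and is a best case. Do not replace it with another fixed figure.
- Report the number of raters and services and the observed ICC.

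The cost is wording and a few lines of Stata, which the study already uses. Intervals will be slightly wider. The administrator or service identifier must be in the analysis dataset. The quality panels choose files to obtain "a spread of KMMS/DMT results, antenatal and postnatal women, health professionals, and health services", which suggests that this information is available, but the article does not say that it is held in the analysis data, so this should be confirmed.
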